## Methods

### Study Setting

This multicenter, interventional cohort study will involve first-year orthopedic trainees stationed in New Zealand hospitals between 2019 and 2023.

Trainee performance will be collected across hospitals located in Invercargill, Rotorua, Timaru, Palmerston North, Whanganui, Taranaki, Tauranga, Christchurch, Waikato, and Auckland for 2022. The locations of first-year trainees in 2023 are yet to be determined. Retrospective comparator performances will be collected through training logbooks and electronic patient records.

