### Recruitment

Intervention group trainees will be approached at training weekends to inform them about the study, to assess eligibility, and to receive consent. Comparator group trainees will be identified from the New Zealand Orthopaedic Association trainee registry and approached via email for this process. Enrollment for comparator group trainees will begin in February 2022, and enrollment for intervention group trainees will occur in the March training weekends of 2022 and 2023.

We aim to include data for 14 trainees in 2022; however, the number of trainees in 2023 is not yet known. The comparator cohort data will be retrospectively audited from trainees who undertook traditional training without exposure to the simulator during their 6 months of follow-up in the years 2019, 2020, and 2021 (n=41). We expect a total sample size of approximately 65 trainees, given an average of 12 new trainees per annum. The comparator group is matched based on their length of registered training at the start of follow-up, that is, first-year trainees with 2 months of registered training.

The in-theater performances of the comparator and intervention groups will be compared using cumulative sum charts for each of the primary outcomes to determine any differences in trends of skill acquisition according to the method of training. The simulator performance of the intervention group will be used to establish a learning curve and compared with in-theater learning curves.

Retrospectively matched trainees have been chosen instead of prospective randomized ones for the comparison group in order to maximize sample size and to avoid contamination. New Zealand only introduces 10-15 trainees per year into the orthopedic training program, and thus a prospective randomized trial will greatly limit the statistical power. There is also the chance of cross-group contamination as there is no way of ensuring comparator trainees located in the same area as intervention trainees will not use the simulator.

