### Interventions and Comparators

#### Intervention

The simulator will be first administered at the March training weekends for each year. We will use these training weekends to test participants at baseline on the simulator and collect demographic data via survey. The simulator will be set up as one of the 15-minute assessment stations in the training weekend. Simulator sets will be distributed to individual trainees following the training weekend. Upon delivery of the simulator sets, the principal investigator will also provide aid to the trainee in identifying an appropriate environment for the simulator and address any setup issues.

It is then expected that trainees will undertake, at minimum, monthly 15-minute practices on the simulator for the next 6 months of training. These practice data are sent to a cloud server after each use. Note that the simulator training will be in addition to any routine training they will receive at their respective hospitals. Over this time, primary end points for each in-theater case will be taken over the course of follow-up through District Health Board (DHB) records, including patient picture archiving and communication system (PACS) records and trainees’ logbooks.

We will request intervention trainees to write out relevant patient data and end point results as the cases present to maximize accuracy. Trainees will be reminded monthly by email to provide case data and practice on the simulator. Their simulator performance will be assessed again in a controlled environment during the November training weekend. At this point, secondary end points will also be collected via survey.

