### Data Collection

#### Outcomes

##### Primary End Points—Collected for Each In-Theater Case Over Follow-up

Theater time and radiation time in seconds (radiation time may not be available from retrospectively assessed notes but will be attained where possible)—collected from procedure reports from electronic patient recordsNumber of fluoroscopy shots—collected from patient PACS recordsPin accuracy—accuracy is defined based on procedural recommendation literature—analyzed from patient PACS recordsComplication/nonideal union incidence—stratified for types of complications (nerve injury, vascular injury, loss of reduction, compartment syndrome, and infection)—collected from reviews of medical records and letters of referral from electronic patient notes

These primary end points have been determined as measurements of trainee performance, which are relatively easily retrieved from patient records and trainee logbooks.

The number of fluoroscopy shots and radiation time can be used to approximate the amount of radiation patients and staff are exposed to. In particular, for patients, theater time and radiation exposure have been shown to correlate to a higher chance of complications and thus should be avoided [21]. Studies have shown a decrease in both measurements for SCHF treatments with increased trainee proficiency [22,23]. Pin accuracy affects the stability of union, and there are well-established guidelines for ideal position of pins.

Ultimately, postoperative complications and nonideal union are the most crucial outcomes the trainees should aim to avoid. We do not expect to see high rates of these for either group, but overall rates will be monitored for comparison.

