### Statistical Analysis

Operative outcomes using data taken before or without ongoing exposure to the simulator will be compared to outcomes using data from trainees who have used the simulator after 1 year. Comparisons will be performed using Student *t* tests or Wilcoxon Rank Sum tests (depending on the distribution of the data) for theater time and chi-square or Fischer exact tests (depending on the count of the outcome) for the number of complications, number of accurate pin placements, and number of mistakes.

Primary end points will be plotted on separate cumulative sum curves to show trends in performance over the course of follow-up by individuals and aggregated according to pre- and post–1-year simulator training. Control limits will be determined based on values identified in the literature and consultation with senior orthopedic consultants [22-24].

Accuracy of pin placements in subsets of images measured twice must be based on anterior-posterior, lateral, and oblique radiographs. Measurements taken will need to be compared for intra- and interobserver reliability using Bland-Altman plots and intraclass correlation scores.

The results from the familiarity questionnaire will be summarized as responses per category.

Univariable ordinary least squares regression analyses will be used to examine the association of theater time, number of complications (including nonideal unions), and number of x-ray shoots with independent variables. Logistic regression will be used to examine the association of accurate pin placement (yes or no) with independent variables. Independent variables will be the number of times the simulator is used, the number of SCHF procedures performed prior to intervention, Gartland classification, scores on tests of spatial awareness, and the number of SCHF procedures performed during the intervention. Independent variables that are significantly associated with a primary end point (*P*<.05) will be included as covariates in multivariable analyses. Appropriate model diagnostics, and where required, data transformations will be used.

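### The named tests and regressions assume independent observations, but outcomes are recorded per case and exposure per trainee; if cases are pooled, P values for trainee-level contrasts are too small

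*Protocol article*

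**What the plan says.** The heading of the primary end points describes them as "Collected for Each In-Theater Case Over Follow-up". The Intervention section agrees: "primary end points for each in-theater case will be taken over the course of follow-up". Exposure is defined by trainee. Under Study Design and Recruitment, a trainee belongs to the simulator cohort (2022-2023) or to the comparator cohort (2019-2021), and all of that trainee's follow-up cases go with that cohort.

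The Statistical Analysis section names Student t tests or "Wilcoxon Rank Sum tests (depending on the distribution of the data) for theater time and chi-square or Fischer exact tests" for complications, accurate pin placements and mistakes. Theater time, complications and x-ray shots are then modelled by ordinary least squares, and for pin accuracy "Logistic regression will be used to examine the association of accurate pin placement (yes or no) with independent variables". The independent variables include Gartland class. Those with P below .05 go forward to multivariable models.

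On size, Recruitment says: "We expect a total sample size of approximately 65 trainees, given an average of 12 new trainees per annum". The trainees are spread over many centres: "Trainee performance will be collected across hospitals located in Invercargill, Rotorua, Timaru" and others.

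The article mentions no trainee effect, cluster-robust variance, GEE, mixed model or per-trainee summary.

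**The concern.** Cases done by one trainee, at one hospital and under the same supervisors, tend to resemble each other. The protocol relies on this itself, since it plans learning curves for individual trainees. A test that counts every case as a separate independent observation then understates the standard error of any contrast between trainees. The contrast that matters most, simulator cohort against comparator cohort, is of that kind.

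At stake is a false claim that the simulator works. The Conclusions section expects the pilot to show efficacy as well as feasibility, so the error rate of the cohort comparison matters even in a pilot.

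This is not a detail left to a fuller document. The article makes a definite choice of methods, and for repeated cases per trainee that choice is unsuitable.

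**Working it through.** **Number of clusters.** Recruitment gives 41 comparators, and about 12 new trainees a year for two intervention years: 41 + 2 × 12 = 65, which reproduces the stated total. The section also says: "We aim to include data for 14 trainees in 2022; however, the number of trainees in 2023 is not yet known". Using 14 for 2022 and 12 for 2023 gives 41 + 14 + 12 = 67, which is close to the same total. I use 41 and 24.

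**Unit of analysis.** The section never states it. Three features point to cases or pins:

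- A trainee with several cases has no single yes/no value for pin accuracy.
- Gartland class describes one fracture, not a trainee.
- Chi-square and Fisher tests on complications and accurate pins work on tallies of cases or pins.

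**Assumptions.** The protocol gives neither the cases per trainee (m) nor the trainee ICC. I take m from 2 to 15 and ICC from 0.02 to 0.30, with a two-sided 5% level.

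**Formulas.**

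- Design effect: DE = 1 + (m − 1) × ICC.
- Actual type I error of the case-level test: 2 × [1 − Φ(1.96/√DE)].
- Effective number of cases: 65 × m / DE.

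**Example, m = 5 and ICC = 0.10.** DE = 1 + 4 × 0.10 = 1.40. The 65 × 5 = 325 cases are worth 325/1.40 = 232. 1.96/√1.40 = 1.66, so the type I error is 9.8%.

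The last column simulates a case-level t test with no true effect, 41 against 24 trainees, Poisson-varying case numbers and 4,000 runs per setting.

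| m | ICC | DE | Cases | Effective cases | Type I error, formula | Type I error, simulated |
|---|---|---|---|---|---|---|
| 2 | 0.02 | 1.02 | 130 | 127 | 5.2% | 5.6% |
| 4 | 0.05 | 1.15 | 260 | 226 | 6.8% | 7.6% |
| 5 | 0.10 | 1.40 | 325 | 232 | 9.8% | 10.6% |
| 8 | 0.10 | 1.70 | 520 | 306 | 13.3% | 13.7% |
| 8 | 0.20 | 2.40 | 520 | 217 | 20.6% | 22.4% |
| 15 | 0.30 | 5.20 | 975 | 188 | 39.0% | 39.1% |

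In the same simulations, a t test on one mean per trainee rejected in 4.7% to 5.3% of runs.

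**If accuracy is scored per pin.** Assume 2 pins per case, 5 cases, ICC 0.10 shared by all pins of a trainee, and 70% accuracy. A chi-square test on pins then rejected in 15.9% of null runs. A t test on one proportion per trainee rejected in 5.1%.

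**The case against.** The strongest reply is that the section does not state the unit. A t or Wilcoxon test on one summary per trainee would be valid, and some of the listed covariates, such as the number of simulator sessions, are trainee-level. That stands as a caveat, and it is why the point is conditional on pooling. It does not remove the point. The yes/no pin outcome and Gartland class do not fit a one-row-per-trainee analysis, so the section would still need correcting if that were the intention.

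A second reply is that this is a pilot, and that Recruitment compares the cohorts by cumulative sum charts. The charts by individual show each trainee's trend, but they do not correct any P value. The difference-in-difference analysis under Strengths and Limitations is named without a model or a clustering term.

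Several stronger readings are tempting, and the document does not support them:

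- *The effective sample is about the number of trainees.* Not in general. At 4 cases and ICC 0.05, 260 cases are worth about 226, far nearer 260 than 65.
- *The error exceeds 5% for every primary end point.* Not shown. No group test is named for fluoroscopy shots or radiation time. Complications are expected to be infrequent, and Fisher's exact test is conservative with sparse counts.
- *Pins are analysed as independent units.* The text does not say whether accuracy is scored per pin or per case.
- *Confidence intervals are too narrow.* The article mentions none. Any taken from the same models for trainee-level contrasts would share the fault.
- *The covariate screen is always too lenient.* That applies to trainee-level covariates when the ICC is positive. For Gartland class, which varies within a trainee, the error can go either way.
- *Busy trainees wrongly dominate.* A pooled test does weight by case number, but that is a choice of estimand and not in itself an error.

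The number of mistakes is a simulator measure, and secondary outcomes are not collected for comparators, so it lies outside this point.

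**Conclusion.** The point holds in conditional form. The named methods do not allow for repeated cases per trainee, and the wording implies that cases are pooled. If they are, P values for cohort and other trainee-level contrasts are too small whenever trainees contribute several positively correlated cases.

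The size cannot be read from the protocol. It rests wholly on the assumed m and ICC, and the 40% end is the extreme corner of that range. With one case per trainee, or an ICC of zero, there is no inflation. The Conclusions section itself refers to lower case volumes in some localities, so the lower part of the range is a real possibility.

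**What to change.** Rewrite the Statistical Analysis section so that the trainee is the unit of inference. Either of two routes will do:

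- Mixed models or GEE with a trainee effect and a small-sample correction, for theater time, fluoroscopy shots and pin accuracy. If accuracy is scored per pin, allow for several pins per case.
- One summary per trainee, compared by a t, Wilcoxon or permutation test.

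State the unit for each outcome. Use the same trainee-clustered models for the regressions and the covariate screen. Report complications descriptively or by a trainee-level permutation test. A hospital effect is optional, if it can be estimated. With about 24 intervention trainees, a model with several nested random effects may not be estimable, so the trainee effect comes first.

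The cost is revised wording and a little more R programming, with no new data. P values will be less favourable than under the pooled tests.

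### Cohort trends are to be compared on CUSUM charts whose only stated reference is external control limits, which cannot show whether the cohorts differ

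*Protocol article*

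**What the plan says.** Three places in the protocol article bear on this.

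- **Methods, Recruitment** gives the charts a between-cohort purpose. In-theater performances of the two groups "will be compared using cumulative sum charts for each of the primary outcomes to determine any differences in trends of skill acquisition" by training method.
- **Methods, Statistical Analysis** describes the charts. End points are "plotted on separate cumulative sum curves to show trends in performance over the course of follow-up by individuals and aggregated according to pre- and post–1-year" exposure to the simulator. The next sentence gives the only reference for reading them: "Control limits will be determined based on values identified in the literature and consultation with senior orthopedic consultants". Nothing there contrasts the two curves, and no limit is set from the comparator cohort.
- **Discussion, Strengths and Limitations** announces a difference-in-difference analysis of the two groups' learning curves, to explore simulator effects. It gives no model, and neither Methods section refers to it.

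Statistical Analysis also plans t or Wilcoxon tests, chi-square or exact tests, and regressions on a list of independent variables.

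**The concern.** The Recruitment section asks whether trends differ by training method, so the null hypothesis is that the cohorts do not differ. A limit taken from published values and consultant opinion serves another null: that this cohort performs at the external standard. Whether a chart crosses depends on how far New Zealand first-year trainees are from that standard and on how many cases the chart contains. Neither is the simulator effect.

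Two misreadings become possible. Two equal cohorts can give one crossing and one non-crossing by chance, which looks like a difference. If both cohorts are worse than the standard, both charts cross and a real difference does not show.

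The other analyses in the Methods do not fill the gap. The two-group tests compare overall levels, not trends. The regressions include the number of simulator uses and each trainee's count of procedures, but no cohort term, no case order and no cohort-by-case-number interaction.

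**Working it through.** **Inputs from the article.** The comparator cohort is 41 trainees. The expected total is stated as "We expect a total sample size of approximately 65 trainees, given an average of 12 new trainees per annum". This reproduces: 41 + 2 × 12 = 65. The intervention cohort is then 65 − 41 = 24, which is derived, not printed. Recruitment also says "We aim to include data for 14 trainees in 2022; however, the number of trainees in 2023 is not yet known"; 14 + 12 = 26 would give 67.

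**Assumed, because the article gives none of it.** A yes/no failure per case, 3, 6 or 10 cases per trainee, independent cases, a constant failure rate, and each cohort's cases placed in one running sum. The chart signals failure against acceptable/unacceptable rates p0/p1 = 10%/20%, with limit h = 2.89 or 4.55.

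**Chart.** S = max(0, S + w), signalling when S > h, where
- w = ln(p1/p0) = ln 2 = 0.693 for a failure
- w = ln((1 − p1)/(1 − p0)) = ln(0.8/0.9) = −0.118 for a success

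The mean step at true failure rate p is 0.693p − 0.118(1 − p). With 6 cases per trainee the charts hold 41 × 6 = 246 and 24 × 6 = 144 cases, a ratio of 1.71.

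**Equal cohorts, both at 15%.** The mean step is 0.104 − 0.100 = 0.004, a total drift of about 0.9 over 246 cases and 0.6 over 144. Both are far below 4.55, so chance decides a crossing. Simulation at h = 4.55:
- comparator chart crosses in 63%, intervention chart in 39%
- exactly one crosses in 53% (comparator only 39%, intervention only 14%)
- a two-proportion z test on the same data rejects in 5%
- with 3 or 10 cases per trainee, exactly one crosses in about 36% or 43%
- with 24 trainees in each cohort and 6 cases, exactly one still crosses in 47%, so unequal chart length is not the main cause

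With both cohorts at the acceptable 10% and h = 2.89, exactly one crosses in about 41%. With both far above the standard, both cross and the figure falls to about 0.

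**Real difference, 35% versus 21%, 6 cases.**
- comparator mean step 0.2426 − 0.0766 = 0.166; × 246 = 40.8
- intervention mean step 0.1456 − 0.0930 = 0.0525; × 144 = 7.6

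Both totals exceed either limit, so both charts are expected to cross. In simulation both crossed in 92% to 99%, and exactly one in 1% to 8%. The z test had about 84% power. For 30% versus 20% the figures are 3% to 13%, against 59% to 60%.

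**Continuous outcome.** Standardised CUSUM, reference value 0.5, h = 4 or 5, 3, 5 or 10 cases, within-trainee correlation 0 or 0.2, equal cohorts of 41 and 24. Exactly one chart crossed in:
- 17% to 52% on target
- 4% to 53% at 0.25 SD off target
- 0% to 19% at 0.5 SD off target

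A direct test on trainee means rejected in 4.5% to 5.8% throughout.

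**Direction.** Keep 10%/20%, h = 4.55, 6 cases and both cohorts at 15%.
- Failure-signalling, 41 versus 24: comparator only 39%, intervention only 14%.
- Proficiency-signalling (weights reversed), 41 versus 24: comparator only 37%, intervention only 13%. The longer chart now favours the comparator.
- Failure-signalling, with only the 8 comparators recruited by February 2022, against 24: intervention only 36%, comparator only 3%.

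With 3 cases per trainee and both cohorts at 10%, the proficiency chart gave 53% and 7%. The 0% to 53% range therefore describes failure-signalling charts, not every design.

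**The case against.** The strongest reply is that the article never makes a limit crossing the decision rule. Comparing on charts and showing trends both fit a descriptive reading of curve shape, with limits marking proficiency, and this is a self-described pilot. That stands. A reader might take 53% as the trial's false-positive rate; it is the error rate of a reading the text permits but does not prescribe. Comparison by eye, however, has no defined error rate either.

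Second, the Discussion plans a difference-in-difference analysis, which is a between-cohort look at learning over time. That also stands, and the charts are not the only comparison. An article may leave model detail to a fuller document. What the article does fix is the charts as the means of determining trend differences, with no link to that analysis.

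Third, one running sum per cohort is assumed. Aggregating by case number, or reading individual charts, removes the length effect. True, but chance gaps remain. In one simulated setting 29% of trainees in each cohort crossed on average. The standard error of the difference is √[0.29 × 0.71 × (1/41 + 1/24)] = 0.117, and the two proportions differed by at least 10 points in 39% of trials.

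A reader might also infer a bias towards the simulator because the comparator chart is longer. The article does not support this: it gives neither the chart's direction nor its aggregation, and final enrolment was open.

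**Conclusion.** The concern holds in a limited form. The Recruitment section asks the charts a between-cohort question, and the only reference supplied answers a different one. Discordant or concordant crossings are not evidence for or against a cohort difference.

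The size is conditional on assumed case numbers, failure rates, limits and aggregation: about 0% to 53% discordance for equal cohorts on failure-signalling charts, and 1% to 8% separation of a real 35% versus 21% difference. The 84% power quoted against that is for a test of levels with independent cases and a constant failure rate. It is not the power of a trend test, which would have to be worked out separately.

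No lean towards the simulator should be claimed, nor that the plan will declare a benefit from a crossing. The planned level tests and the exploratory difference-in-difference analysis soften the consequence, but they do not give the charts a valid between-cohort reference. This is worth correcting before the cohorts are compared.

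**What to change.** In Recruitment and Statistical Analysis:

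1. Keep the CUSUM charts and external limits as description of when trainees reach a proficiency standard. State that crossing or not crossing is not evidence for or against a cohort difference.
2. Plot cohort curves as the mean per trainee by SCHF case number, so that curve height does not depend on cohort size.
3. Make the difference-in-difference analysis the stated trend comparison, as an explicit model: outcome on cohort, case number and cohort × case number, with a trainee random intercept. Use a linear model for theater time, a count model for fluoroscopy shots and a logistic model for pin accuracy. Alternatively, take the reference band for the gap between mean curves by permuting cohort labels across trainees.

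The cost is revised wording and a little R code on data already being collected, with no new participants. The downside is that the interaction estimate will be imprecise with few cases per trainee, so the trend result will look less decisive than a chart that crosses a line.

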**Methods:**

This multicenter, interventional cohort study will involve orthopedic trainees from New Zealand in their first year of advanced training between 2019 and 2023. Advanced trainees with no simulator exposure who were in their first year in 2019-2021 will form the comparator cohort, while those in the years 2022-2023 will receive additional regular simulator training as the intervention cohort. The comparator cohort’s performance in pediatric SCHF surgery will be retrospectively audited using routinely collected operative outcomes and parameters over a 6-month period. Data on the performance of the intervention cohorts will be collected in the same way over a comparable period. The data collected for both groups will be used to determine whether additional training with an augmented reality training shows improved real-world surgical outcomes compared to traditional surgical training.

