### An Alternative Training Method

Improvements in computer technology have afforded the development of a new method of surgical training—augmented reality (AR) simulation. Using AR technology, skill acquisition can take place before entering the operating room. CRPP requires a high level of hand-eye coordination, visuospatial reasoning to interpret the X-ray image, and haptic interpretation to be able to feel the wire entering or leaving the bone. One such example was developed by our research team. The “BoneDoc AR” simulator (University of Otago) that we have produced uses an iPad app to provide real-time simulated X-ray images, while trainees are drilling through a physical model of the elbow. This physical model is made of silicone soft tissue and 3D-printed plastic bones. In addition, the simulator can provide objective measures of proficiency, such as exact pin placement, which are not possible without the use of computed tomography scans. These objective measures may be of value in providing feedback on skills acquisition during surgical training. 

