### Study Overview

Appropriate validation of the BoneDoc AR simulator is necessary to determine its usefulness in surgical training. Transfer validity, the ultimate test of a surgical simulator, is the transfer of skills acquired on a simulator into the real-world operating theater. Validity tests are necessary to ensure the efficacy of a simulator in a training environment [19]. There are few surgical AR simulators, which have shown positive transfer validity, and none on AR simulators of SCHF treatment [20]. There is a clear paucity in the literature of this field, and there is a need for further research. This pilot study aims to examine the transfer validity of orthopedic trainee practice on the BoneDoc AR simulator.

We hypothesize that training with the simulator will improve in-theater performance as defined by a reduction of theater time, number of fluoroscopy images taken, postsurgical complication rates, and an increase in pinning accuracy. In all metrics, intervention trainees will be compared with retrospective-matched comparator trainees.

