### Data Management

Adverse events are unexpected with the use of the simulator, as trainees have operative experience and there is a low infection risk. Nevertheless, an independent data monitoring committee (DMC) has been setup consisting of 2 clinicians and will be reported to by a study researcher. Any adverse events will be reported immediately to the committee by trainees directly, and the committee may request an interim analysis of the data collected up to that point. The committee can request that the study be paused or discontinued based on the data they receive. The DMC will meet every 6 months to discuss this project.

Study researchers will ensure that the participants’ anonymity is maintained. The participants will be identified only by a participant’s ID number. Individual patients will not be contacted by a researcher. Identifiable patient and participant data will be anonymized and stored on secure University of Otago servers, and will only be accessible by the researchers directly involved with this data collection. Analysis will be performed only on anonymized data sets with an anonymous identifier instead of NHI numbers. The study will comply with the Data Protection Act, which requires all data to be anonymized as soon as it is practical to do so. Data will be stored for 10 years after the conclusion of the study and subsequently destroyed.

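### Pin accuracy, a primary end point, is read from radiographs with no stated step that conceals cohort from the readers

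*Protocol article*

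**What the plan says.** The Primary End Points section lists pin accuracy among the primary end points. It takes the data from patient PACS records and says that "accuracy is defined based on procedural recommendation literature".

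The Statistical Analysis section gives what there is on reading: "Accuracy of pin placements in subsets of images measured twice must be based on anterior-posterior, lateral, and oblique radiographs", followed by "Measurements taken will need to be compared for intra- and interobserver reliability using Bland-Altman plots and intraclass correlation scores". The number of accurate placements is then compared between cohorts by a chi-square or Fisher exact test, and the end point is also modeled as a binary outcome: "Logistic regression will be used to examine the association of accurate pin placement (yes or no) with independent variables".

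The cohorts are separated by year. The abstract states that "Advanced trainees with no simulator exposure who were in their first year in 2019-2021 will form the comparator cohort", with the 2022-2023 trainees as the intervention cohort. On the simulator's origin, An Alternative Training Method says "One such example was developed by our research team". The hypothesis in Study Overview is directional and includes, among the expected benefits, "postsurgical complication rates, and an increase in pinning accuracy".

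The nearest safeguard is in Data Management: "Analysis will be performed only on anonymized data sets with an anonymous identifier instead of NHI numbers".

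**The concern.** Trainees cannot be masked to whether they practiced on a simulator, and the Recruitment section gives reasons for not randomizing. Masked reading is therefore one of the few protections against bias still open to this study, and pin accuracy, read from stored images, is well suited to it.

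The quality control that the article does describe is aimed at random reader error: fixed views, repeat measurement of subsets, and agreement within and between observers. Systematic error that runs with cohort is not addressed. If readers can tell the cohort, borderline placements may be called accurate more readily in one cohort than in the other. A difference in favor of the simulator could then arise, or be enlarged, without any difference in surgical performance. A positive finding on this end point would be open to an objection that could have been removed in advance.

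**Working it through.** The article gives no figure to reproduce. The check sets its statements side by side; a labeled illustration follows.

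1. **Is masking stated anywhere?** No section mentions blinding, masking, removal of dates, mixing of cohorts, or readers independent of the developers. The Strengths and Limitations section names the non-randomized design, historical comparators, confounding and record quality, but not assessor bias.

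2. **Could a reader infer cohort?** Surgery in 2019-2021 is comparator and surgery in 2022-2023 is intervention, so a date is enough. Under Patient Data, patient identifiers and surgical details come from trainee logbooks, so whoever retrieves the images from those entries works from trainee to image. The article does not say whether that person is also a reader, or whether the images as read show dates. That they may do so is an assumption.

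3. **Is there a direction for expectation to push?** Yes. The team built the device and expects pin accuracy to increase.

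4. **Would the reliability analysis show it?** No. Bland-Altman plots and intraclass correlations compare one reading of an image with another reading of the same image. If both readers know the cohort and lean the same way, their readings agree and the bias stays in both.

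5. **Does the anonymization prevent it?** As written, it replaces the NHI number in the data sets used for analysis and identifies participants by an ID number. It says nothing about image dates or cohort at the time of reading.

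6. **Illustration only; every input except the trainee counts is assumed.** Let true accuracy be p in both cohorts, and let readers call accurate a share f of the inaccurate intervention cases. The false difference is f × (1 − p).
   - p = 0.80, f = 0.10: 0.10 × 0.20 = 0.02, or 2 percentage points.
   - p = 0.60, f = 0.30: 0.30 × 0.40 = 0.12, or 12 percentage points.

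   The Recruitment section gives 41 comparator trainees and about 65 in total, so about 65 − 41 = 24 intervention trainees. Assume 2 to 5 cases per trainee: 82 v 48 cases (41 × 2, 24 × 2) up to 205 v 120 (41 × 5, 24 × 5). Treat cases as independent. In a two-sided 5% test of two proportions, the chance of a significant result favoring the simulator is Φ[(difference − 1.96 × SE0)/SE1], where SE0 is the pooled and SE1 the unpooled standard error.
   - Smallest case: (0.02 − 1.96 × 0.0717)/0.0709 = −1.70, giving about 4.5%.
   - Largest case: (0.12 − 1.96 × 0.0550)/0.0534 = 0.23, giving about 59%.

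   The nominal value in that direction is 2.5%. The width of this range shows that the inputs, not the documents, set the answer.

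**The case against.** The strongest objection is that this is an argument from silence. The article condenses a fuller protocol, never says that readers know the cohort, and does not say who reads or from what medium. The two sentences on reading concern images measured twice and their agreement statistics, so they are closer to a reliability sub-study than to a full reading procedure. All of this stands. A reader might infer that following the plan as written gives unmasked reads; the text does not support that, because it leaves masking undetermined.

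A reader might also take pin accuracy to be the primary end point most dependent on judgment. The article does not show this. It refers to established guidelines for pin position, and its agreement methods suit quantitative measurements, so the yes/no call may be derived from a measured criterion. Complications and nonideal union, taken from record reviews and letters, may leave as much room for judgment.

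Finally, this is a pilot with several primary end points, and theater time, radiation time and fluoroscopy counts are not touched by this point.

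The objection does not remove the concern. Masked outcome assessment is a core design safeguard rather than a detail usually deferred to an analysis plan. The article chose to describe reading and its quality control for a primary end point, and what it describes can neither prevent nor reveal a shared bias. A measured criterion narrows the room for expectation but does not close it, since small shifts near a cut-off still change a yes/no call.

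**Conclusion.** The concern holds in a limited form. For a primary end point that is read from images, reduced to yes/no and compared between cohorts, the article states no step that conceals cohort from readers. Calendar year reveals cohort, and the team has both a stake in the device and a stated expectation. The conclusion rests on the assumption that readers could see a date or another identifier, which the article neither confirms nor excludes.

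The size of any bias cannot be estimated from the document. The 2 to 12 points in the illustration follow from assumed inputs and should not be read as an expected bias, nor as evidence that bias will occur. The study is not invalidated, but the safeguard should be added because it is available and the planned checks cannot stand in for it.

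**What to change.** State in the protocol that pin accuracy is read masked to cohort, and how:

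- Before reading, remove dates and hospital, patient and trainee identifiers from the images of both cohorts, and assign study codes.
- Pool the cohorts and have the readers already planned assess the images in random order.
- Draw the repeat readings for intra- and interobserver agreement from the same masked set.
- Keep the code key away from the readers, and link readings to cohort only after they are locked.

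No extra patients, images, readers or procedures are needed, and because the images are archived this works for the retrospective cases too. The cost is image preparation across sites (ten locations are named for 2022, and those for 2023 were not yet known). The article gives no basis for putting hours on it, but it should be modest. Reading must also wait until images from both cohorts are available, or proceed in batches that each mix the two. If the full protocol already provides for masked reading, stating it in the article is enough.
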